## **7. Trial Device**

The intervention is a non-invasive BCI system-based games that is unlikely to cause any direct harm and may improve ADHD symptoms.

While the subject play the training game and attempt the MCQ tasks, EEG waves will be recorded through EEG sensors that are connected through Bluetooth technology. The subject wears the headband with EEG sensors placed on the subject's forehead and a clip is attached to the ear lobe for grounding purposes.

## **8. Treatment of Subjects**

### **8.1 Specific Restrictions**

1. There are no dietary restrictions.
2. There is no limitation in the physical activity of the subject.
3. Intake of methylphenidate, atomoxetine and tricyclic anti-depressant are to be avoided 1 month before and during the study since these medications can improve ADHD symptoms. The parent/legal guardian and/or the subject will be asked about this during each study visit. If there is a need for these medications to be prescribed to the subject then the subject will be withdrawn from the study.
4. Intake of polyunsaturated fatty acids (PUFA) supplement intake (e.g. Omega-3 oil, flax seed oil, cod liver oil) which can improve ADHD symptoms are also to be avoided 3 months before and during the study. These supplements are receiving attention as a complementary approach to managing ADHD. While not a primary empirical based treatment and efficacy outcome varied, the study team will exclude subjects who are taking these supplements in the past 3 months, if they have been taking them regularly for a period longer than 2 weeks, to ensure that any improvement in inattentive symptoms is not due to the supplementation.
5. Intake of traditional Chinese medication (TCM) treatment is also to be avoided 1 month before and during study. Similar to PUFA, these alternative treatments could also manage inattentive symptoms. Therefore, subjects will be withdrawn from the study if these supplements are taken in the past 1 month.
6. From the literature, the potential risks to the BCI may include seizure or destabilization of the individual's mood state. To minimize such risk, subjects with history of seizure or severe psychiatric disorder will be excluded in this study.

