### 3.3 Withdrawal Criteria

Subjects may be withdrawn from the intervention according to the discretion of the Principal Investigator if:

1. ADHD-RS raw score increases by 25% as rated by clinicians, and/or
2. CGI-S scores are between 5 and 7 inclusive.
3. Receive any medication (e.g. methylphenidate, atomoxetine, tricyclic anti-depressant, and/or polyunsaturated fatty acids (PUFA) supplement (e.g. Omega-3 oil, flax seed oil, cod liver oil), and/or traditional Chinese medication (TCM) which can improve ADHD symptoms during the trial period. The parent/child will be asked about this each time they turn up at the clinic.

All recruited subjects are free to withdraw consent and discontinue participation without penalty and without providing reasons. However data collection will continue after withdrawal from intervention unless the subject or parents/legal guardians decide to withdraw from the study totally (this will be explicitly asked again upon withdrawal).

Participants can still choose to continue or discontinue with the remaining assessments at Week 1, 8, 16 (control), 20 (intervention), 24 (intervention), 28 (control), and 32 (control) despite having BCI training sessions being ceased.

Subjects will be considered as 'drop-outs' if they:

1. Become lost to follow-up or discontinues intervention.

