### **6.3 Briefing session for all potential subjects**

During briefing sessions, the research team will provide an overview of ADHD and a demonstration of the BCI study will be conducted for parents to view. It will be highlighted that medication and psychosocial treatment represent current evidence-based treatment for this disorder. The BCI study will be presented as an alternative form of treatment that is being investigated in this study and parents will have ample time and opportunity to choose the treatment of preference. At the end of each briefing, parents will be provided with participant information sheets to take home for further consideration of participation.

After the briefings, parents will be contacted within one to two weeks to give all subjects sufficient time to contemplate and ask any queries pertaining to the study. If the parents indicate interest, a session will then be arranged for informed consent to be taken. Informed consent will be obtained from the parents, and assent from the subjects, prior to any form of assessment or intervention as part of the study. The blinded clinician will contact the child's school teacher(s) and obtain feedback about the child's behavior in school at various time points. This will be made known to parents during the briefing session. All trial-related procedures will only take place after informed consent has been obtained. A baseline assessment will be done to determine the child's eligibility for the study.

In the event that the child is eligible but the parents/legal guardians choose not to participate in the study, the parents/legal guardians will be offered an option to have the child be followed-up at the CGC.

Participation is strictly voluntary and at any point if the subject wishes to drop-out, he/she will not be restricted or punished for it.

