## **9.3 Safety Monitoring Plan**

The investigator is responsible for monitoring the safety of study participants who have entered this study and to take appropriate action concerning any event that seems unusual. Subjects will be followed up if:

- Subject has at least one SAE or subject withdrawn from the study as a result of an AE, until the event has been resolved, subsided, stabilized, disappeared, the event is otherwise explained, or the subject is lost to follow up
- Or, in the case of other non-serious AEs, until they complete the study or they are lost to follow up

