## **9.5 Criteria for Stopping the Research**

Subjects are not expected to experience any problems when participating in these training games. There is no invasive procedure involved. The research however may be suspended if any part of the protocol is breached or if there is any violation of standard research ethics.

Parents can undergo a review with the study psychiatrist to consider dropping out of the study if:

1. ADHD-RS raw score increases by 25% as assessed by the clinician and/or
2. CGI scores are between 5 and 7 inclusive.

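### Sections 8.1 and 3.3 give conflicting withdrawal rules for a child who needs ADHD medication, and the literal 8.1 rule could cost the week-8 primary rating

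*Protocol*

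**What the plan says.** Section 8.1 item 3 lists methylphenidate, atomoxetine and tricyclic antidepressants as drugs to be avoided, because they can improve ADHD symptoms. It then sets the consequence: "If there is a need for these medications to be prescribed to the subject then the subject will be withdrawn from the study".

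Section 3.3, which is devoted to withdrawal, opens differently: "Subjects may be withdrawn from the intervention according to the discretion of the Principal Investigator if". Its third criterion begins "Receive any medication (e.g. methylphenidate, atomoxetine, tricyclic anti-depressant" and goes on to PUFA supplements and traditional Chinese medicine. On what happens afterwards it says: "However data collection will continue after withdrawal from intervention unless the subject or parents/legal guardians decide to withdraw from the study totally". On visits it adds: "Participants can still choose to continue or discontinue with the remaining assessments at Week 1, 8, 16 (control", and continues with the later time points.

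The primary endpoint (2.1.2) is the change in the clinician-rated ADHD-RS inattentive score from week 1 to week 8. Section 11.2.3 compares it by a two-sample t test, and 11.2.1 defines the intention-to-treat set as every randomised subject.

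**The concern.** The two sections give different answers for the same child on the same drugs. One is mandatory and removes the child from the study. The other is discretionary, removes the child only from training and keeps the assessments. Section 3.3 itself separates leaving the intervention from leaving the study, and ends data collection only for the second.

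If a need for medication is identified before the week-8 visit and staff follow 8.1 to the letter, the primary rating may never be taken. That child then has no change score, and the t test no longer covers everyone randomised. The loss would not be random: a child who needs medication is likely to have symptoms that are worse or not improving. An analysis plan can decide how to treat a rating taken on medication, but it cannot recover one that was not taken.

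**Working it through.** The main check sets the two rules side by side.

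| | 8.1 item 3 | 3.3 item 3 |
|---|---|---|
| Drugs | methylphenidate, atomoxetine, tricyclics | the same three, plus PUFA and TCM |
| Trigger | a need to prescribe | receipt |
| Force | mandatory | Principal Investigator's discretion |
| Scope | the study | the intervention |
| Later assessments | not mentioned | continue, week 8 named, unless the family withdraws totally |

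**Do the different triggers reconcile the rules?** No. A child prescribed one of these drugs during the trial has first been judged to need it, so 8.1 applies first. Once 8.1 has been applied, 3.3 has no role left for that child.

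**Does other text settle which rule governs?** No. Usage elsewhere is loose. Section 9.5 attaches this to the same symptom triggers as 3.3: "Parents can undergo a review with the study psychiatrist to consider dropping out of the study if". Section 9.3 keeps following, for safety, a "subject withdrawn from the study as a result of an AE, until the event has been resolved". Section 3.3 counts a child who discontinues the intervention as a drop-out, although that child's data collection continues.

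**When does it touch the primary endpoint?** Only when the need is identified before the week-8 rating. Later needs affect the secondary and sustainability endpoints only.

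**How would a need come to light before week 8?** Medication is asked about at each study visit (8.1) or each clinic attendance (3.3).
- Intervention arm: 24 training sessions over 8 weeks (5.1), that is 24/8 = 3 a week, held at the clinic (12.1).
- Control arm: no training until week 9 (5.2), and no assessment between weeks 1 and 8 (6.6), so no scheduled contact.

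A control's medication start would therefore usually surface at the week-8 visit, when the rating is due. An intervention child's would surface sooner. The chance of removal before the rating could thus differ between arms because of how often children are seen, apart from any difference in need.

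**Is power the issue?** No. The inputs are effect size 0.5, two-sided 5% and 80% power (11.1, 11.2.1).
- Plan's own figure: n = 2 × (1.960 + 0.842)² / 0.5² = 62.8, so 63 per group; 63/0.8 = 78.75, so 79. By the exact t test, 64 per group; 64/0.8 = 80. The stated figure of about 80 is reproduced.
- With 86 enrolled per arm, power is 0.903 with no loss and 0.829 at 20% loss (86 × 0.8 = 68.8 per arm). It is still 0.801 at 64 per arm, which is 86 − 64 = 22 losses, or 25.6%.

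The sample size absorbs the planned losses. What it cannot repair is a loss related to the outcome.

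**The case against.** The best defence is that 3.3 is the operative rule. It is the dedicated withdrawal section, names the same drugs, and makes a family decision the only route it states to ending data collection. Section 8.1 is a list of restrictions; it never says that assessments stop, and leaving the study is not a defined term. Staff could reasonably read 3.3 as controlling. This stands in part: loss of the week-8 rating is an inference, not something the protocol states. But 8.1 is worded as mandatory and has no clause preserving assessments, and a trial should not depend on staff setting a mandatory rule aside.

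The second defence is that few children would be affected. Families hear about medication before joining, and under 6.3 "parents will have ample time and opportunity to choose the treatment of preference". Controls are promised training from week 9 and have no scheduled contact before week 8. This also stands, and it limits the point.

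A reader might infer that waiting controls would start medication more often and be lost, so that the bias has a known sign. The documents do not support that. No rate of medication starts is given, and the contact schedule suggests that intervention children could be the ones more readily detected and removed.

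A third objection is that ratings taken on medication blur the comparison, which is why 8.1 restricts these drugs. That is a real cost of the fix. It can be handled in the analysis once the rating exists.

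**Conclusion.** The contradiction is in the text and should be resolved. The two rules differ in force and in scope for the same drugs, and nothing says which prevails. The consequence is conditional on three things: a need arises before the week-8 visit, it is identified before the rating is taken, and staff apply 8.1 as written. The primary rating may then not be collected, for a reason related to symptoms.

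The frequency, size and direction of any bias cannot be estimated from the protocol, and the number of children may be small. Two stronger readings go too far. One is that the week-8 rating is certain to be lost; 8.1 does not say so, and 3.3 points the other way. The other is that TCM use in 8.1 item 5 raises the same conflict. Its one-month look-back reads more like the TCM exclusion criterion in 3.2 than a rule for use during the trial, so it is not relied on here.

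**What to change.** In 8.1 item 3, replace removal from the study with the 3.3 rule. If one of these drugs is needed or taken, BCI training may be stopped (or, for a wait-list child, not started) at the Principal Investigator's discretion. All scheduled assessments, including week 8, continue in both arms unless the family withdraws from the study totally.

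The cost is one amended sentence and ethics board approval of the amendment (Section 12). The visits are already in the schedule in 6.6. The statistical downside is that some week-8 ratings will be taken on medication that can improve symptoms. These could dilute the difference if more controls are medicated, or distort it the other way if more intervention children are. The medication record that 8.2 requires on the case report form identifies these children, so a sensitivity analysis is possible; its form can be left to the SAP.

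The reference in 8.2 to section 9.1 item 3 should read 8.1 item 3. That is clerical and can be corrected in the same amendment.

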### **8.2 Concomitant Medications**

To ensure that the subjects are not taking any of the above mentioned restricted drugs (see above section 9.1. item 3), all restricted medications taken within 1 month prior to screening visit and during

the entire study period will be recorded in the Concomitant Medications section of the Case Report Form (CRF).

### **8.3 Unblinding**

Unblinding of the clinician is only allowed in cases of emergency.

## **9. Safety Measurements**

### **9.1 Definitions**

#### **9.1.1 Adverse Events**

The Pediatric Adverse Event Rating Scale will be used to assess adverse events.

#### **9.1.2 Unanticipated Problems Involving Risk to Subjects or Others**

Unanticipated Problems Involving Risk to Subjects or Others (UPIRTSO) events refers to problems, in general, to include any incident, experience, or outcome (including adverse events) that meets ALL of the following criteria:

1. Unexpected

In terms of nature, severity or frequency is not consistent with –

- a. the research procedures that are described in the protocol-related documents, such as the DSRB approved research protocol and informed consent document; or
- b. the characteristics of the subject population being studied

2. Related (including possibly related) to participation in the research

Possibly related means there is a reasonable possibility that the incident, experience, or outcome may have been caused by the procedures involved in the research.

The following conditions might help assess causality:

- a. the event has a reasonable temporal relationship to the intervention,
- b. the event could not have been produced by the underlying disease states,
- c. the event could not have been due to other non-study interventions,
- d. the event follows a known pattern of response to the interventions, or
- e. the event disappears with cessation of intervention.

An event need not be serious to qualify as reportable.

#### **9.1.3 Serious Adverse Events**

A serious adverse event (experience) or reaction is any untoward medical occurrence that at any dose:

- results in death,
- is life-threatening,

- requires inpatient hospitalisation or prolongation of existing hospitalisation,
- results in persistent or significant disability/incapacity, or
- is a congenital anomaly/birth defect.

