### 2.3.1 Safety Endpoints

Adverse events and serious adverse events.

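### The five-outcome definition of a serious adverse event can leave a seizure or mood destabilisation, the BCI risks the protocol itself names, classed as non-serious, and 7-day reporting of these events is ambiguous

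*Protocol*

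**What the plan says.** The safety endpoint in Protocol 2.3.1 is "Adverse events and serious adverse events", and 2.2.1 makes safety concerns about BCI a secondary objective.

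Section 9.1.3 opens with "A serious adverse event (experience) or reaction is any untoward medical occurrence that at any dose" and then lists five outcomes: "results in death"; "is life-threatening"; "requires inpatient hospitalisation or prolongation of existing hospitalisation"; disability or incapacity that is either persistent or significant; and congenital anomaly. The list ends there. No other section adds a seriousness criterion or names events that are always treated as serious.

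Section 8.1 item 6, citing the literature, states that "the potential risks to the BCI may include seizure or destabilization of the individual's mood state". Its response is to exclude children with a history of seizure or severe psychiatric disorder.

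Section 9.1.2 defines a UPIRTSO as an incident, experience or "outcome (including adverse events) that meets ALL of the following criteria", namely unexpected and at least possibly related. It adds that seriousness is not needed for an event to be reportable. Section 9.2.2 sets 24 hours for local deaths and 7 calendar days for all other problems.

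Section 9.3 follows a child with an SAE, or one withdrawn from the study because of an AE, until the event has settled or been explained, or the child is lost. Other non-serious AEs are followed to study completion or loss.

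Section 9.5 says "Subjects are not expected to experience any problems when participating in these training games".

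**The concern.** The protocol names two harms that might come from the device, and its definition of a serious event is not built to catch either of them. A brief first seizure during training, or a mood episode handled without admission, can pass through 9.1.3 without meeting any listed outcome.

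Three things then depend on that label or on a related judgement:

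- what is counted in the SAE half of the safety endpoint;
- how long the event is followed when the child stays in the study;
- whether the event is reported within 7 days, which depends on expectedness, not on seriousness.

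The trial could truthfully state that it had no SAEs although a child had a seizure that was possibly related to the device. A reader of the safety result would not expect that, given that the protocol names seizure as a risk.

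**Working it through.** This is a check of definitions. The protocol gives no event rates, so there is no figure to reproduce.

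**1. The named risks against the five outcomes.** Take a first seizure, or a mood destabilisation, that is managed without admission and leaves no significant incapacity.

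| Outcome in 9.1.3 | Met? |
|---|---|
| Death | No |
| Threat to life | No, unless the particular episode was life-threatening |
| Hospitalisation, new or prolonged | No, not admitted |
| Persistent or significant disability or incapacity | No, although a significant transient incapacity could qualify |
| Congenital anomaly | Not applicable |

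Such an event meets 0 of 5 and is a non-serious AE.

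**2. Who could have one.** The exclusions in 8.1 item 6 remove children with a prior history. They do not prevent first events. All subjects are eventually due to receive BCI (section 5), so the planned exposed group is 86 + 86 = 172 (5.1, 5.2).

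**3. Effect on follow-up (9.3).** As an SAE, the event is followed until it settles, is explained or the child is lost. As a non-serious AE in a child who stays in the study, it is followed to study completion. From the visit weeks in 6.6:

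- Event around the post-booster visit: 24 − 20 = 4 weeks remain in the intervention group, and 32 − 28 = 4 weeks in the control group.
- Event at the start of training: 24 − 1 = 23 weeks remain in the intervention group, and 32 − 9 = 23 weeks in the control group.

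The difference therefore matters most for events late in the booster phase.

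**4. Effect on reporting (9.1.2, 9.2.2).** The reporting deadlines stand only under UPIRTSO. A non-fatal event falls under the 7-day limit if it is both unexpected and at least possibly related. Expectedness is judged against (a) the procedures described in protocol-related documents or (b) the characteristics of the population.

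- *Towards expected:* 8.1 item 6 names both events as potential risks, so an assessor could find them consistent with (a).
- *Towards unexpected:* children with a history of seizures are excluded, so a first seizure fits poorly with (b). Section 9.5 says no problems are expected, section 7 calls direct harm unlikely, and section 15 expects no injury.

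The (b) argument is stronger for seizure than for mood, because only severe psychiatric conditions are excluded. The sentence that waives seriousness does not settle the matter, since it does not waive unexpectedness.

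**5. Effect on the count.** If no other SAE occurs, reclassifying one such event changes the result from 0/172 to 1/172 = 0.0058, or 0.6%. This assumes that all 172 children are treated.

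**The case against.** The case for leaving the text alone has real substance, and several parts of it stand.

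- **The event is not lost.** Section 9.2.1 collects AEs from consent to the end of the study, 2.3.1 counts AEs as well as SAEs, and 11.2.3 tabulates AEs for the pooled treated sample. No SAE comparison or SAE-based stopping rule is stated. A reader might infer that a seizure could vanish from the results. The documents do not support that: it would appear as an AE and be missing only from the SAE count.
- **Seriousness starts no reporting clock.** A reader might infer that a non-serious label means no expedited report. It does not. Apart from the 24-hour rule for deaths, 9.2.2 depends on the UPIRTSO test, which covers non-serious events. Adding a category to 9.1.3 alone would change no deadline.
- **The UPIRTSO route may well work.** With seizure history excluded, a first seizure is plausibly unexpected under limb (b) and so reportable in 7 days. That is a fair reading, but the text does not compel it.
- **Withdrawal for an AE already brings the longer follow-up.** The shorter follow-up concerns only a child who stays in the study.
- **Sections 8.1 and 9.5 do not strictly contradict each other.** A risk can be possible and yet not expected after exclusions. They do pull in different directions on expectedness, which is the very judgement that decides reporting. With a single site (6.4), the risk is disagreement between assessors, not between sites.
- **Nothing in the protocol demands a sixth category,** and mood destabilisation is not defined. Both are true. The case for the change rests on the mismatch between the named risks and the definition, not on an outside rule.

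**Conclusion.** The point holds in a limited form. As 9.1.3 is written, a seizure or mood destabilisation is non-serious unless it is fatal, life-threatening, leads to or prolongs a hospital stay, or causes persistent or significant disability or incapacity. The consequences are an SAE count that can omit the harms the protocol itself names, shorter follow-up for a child who remains in the study, and reporting that is ambiguous rather than absent.

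The size cannot be put as a rate, because the documents give none. With few events, a single classification decides whether the SAE result is zero. The primary endpoint, the sample size and the efficacy analyses are not affected.

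Two assumptions are involved. The event must truly fall short of all five outcomes. Its appearance in the AE table also assumes that the side effect checklist cited in 11.2.3, whose items are not shown, captures it. This is a cheap improvement, not a fault that undermines the trial.

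**What to change.** Three wording changes:

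1. In 9.1.3, add important medical events as a sixth category and name seizure and mood destabilisation as classified there. The investigators should state what counts as mood destabilisation, so that the new category does not bring its own variability.
2. In 9.1.2 and 9.2.2, state that these two events, when possibly related, are reported within the existing 7-calendar-day limit whether or not they are judged expected. This sentence is needed separately, because the change to 9.1.3 does not affect reporting.
3. Align the sentence in 9.5 with 8.1 item 6, so that the protocol gives one consistent account of what is anticipated.

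These changes concern classification and reporting only. How such events are managed clinically is left to the investigators. The cost is about three sentences in an amendment, possibly a few more reports, and an SAE count that may look less favourable.
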